**Bias**

To minimize the biases the maximum efforts will be taken by careful selection of subjects that represent the source population, maximizing response and follow-up rates, standardization of data collection process, provision of training for the data collectors and supervisors, and randomization. To decrease loss to follow-up, study participants will be reminded by WDA facilitators 2 days before the CLHEI date.

**Statistical data analysis**

Data will be entered into Epidata version 3.1 and exported to the Statistical Package for Social Science (SPSS) version 25 and Stata version 14 for further processing and analysis. During the analysis, all quantitative variables will be handled by recoding, calculations, and categorizations before carrying out the main analysis. Descriptive analyses will be carried out to get descriptive measures for the important variables of interest. The descriptive statistic techniques will be utilized for the data organization and presentation. All continuous data will be checked for the normal distribution. If approximately normal distributed the mean and SD will be reported. The missing data will be handled by using multiple imputation methods. The Principal Component Analysis (PCA) will be carried out for the computation of the wealth index. The effect of clustering will be checked by using an Intra-Cluster Correlation Coefficient (ICC) value. The multilevel analysis will be considered if the calculated value of ICC is greater than 5%. Before conducting a multilevel analysis, we will decide whether or not the multilevel model is required by doing a random intercept model. This model offers data regarding ICC which is utilized to determine whether a multilevel model is required or not. If the chi-square test is significant or the ICC value is greater than 5%, the multilevel analysis model is mandatory to consider. Both bi-variable and multivariable analyses using generalized mixed models with random effects will be carried out. The Generalized Estimated Equations (GEE) or multilevel regression models will be utilized to adjust for between and within-cluster variation for adjusted analysis. Those variables with p-values < 0.25 on the bi-variable analysis model will be included in a multivariable regression model to find out predictors independently associated with MHSU adjusting for other variables in the model. The candidate variables will be entered into the multivariable regression model using the ENTER regression method. The basic assumptions of generalized mixed models will be tested before proceeding with the analysis. The stratified and multivariable analyses will be used to control for the potential confounding variables. Effect modification will be examined using stratification and entering effect modifiers into the multivariable analysis model one at a moment. Multicollinearity among the independent variables will be also evaluated using a multiple linear regression model. The variance inflation factor (VIF) < 10 and tolerance statistics > 0.1 will be used to declare the absence of multicollinearity. The presence and strength of a statistically significant association between MHSU and the independent variables will be assessed using adjusted odds ratios (AORs) with a 95% CI. A statistically significant association between the variables of interest will be confirmed when the 95% CI of the AORs did not contain 1. All analyses of the study will be carried out using a 95% CI or 5% level of significance. Though, a statistical significance level will be adjusted to account for the effect of multiple comparisons problem using the Bonferroni corrections methods. The adjusted level of significance is computed by dividing the preset level of significance by the number of statistical tests conducted (outcome variables). In our case, the adjusted level of significance is 0.05/3 = 0.017. Thus, a statistically significant association will be declared when p-value less than 0.017. After the finish of the qualitative data collection, the tape-recorded data will be transcribed verbatim of the local language and translated to English. The coding and analysis of the qualitative data will be done using the thematic content analysis technique by Atlas-Ti software and presented in narratives. A paired t-test will be utilized to measure the mean change from baseline for both groups (intervention and control) groups. Then, an independent t-test will be utilized to compare the mean change of women’s knowledge regarding ODS and BPCR practice scores and MHSU for interventional groups against the mean change of the control group as effect size. To assess the effect of HEI on maternal knowledge regarding ODS and BPCR practice scores and MHSU, an intention-to-treat analysis will be done to compare outcomes between the two groups.

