**Study design**

A community-based cross-sectional study, phenomenological qualitative study, and parallel-group Cluster Randomized Controlled Trial (CRCT) will be used to address the objectives of the current study. The study is a 2 arm CRCT, with every cluster being *kebeles* located in the Dale and Wonsho districts of Sidama region, Ethiopia. The hallmark of this design is each cluster remains in the arm it was randomly assigned to during the course of the whole study period. Thus, all study subjects are randomly assigned into a group and all the study subjects in the assigned group obtain or do not obtain an intervention.

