**Sample size calculation**

The adequate sample size for all objectives is calculated using openepi version 3 software. The sample size needed to estimate the utilization of MHS is calculated assuming the anticipated utilization of ANC (74%), births attended in an HF (48%), and PNC (34%) according to the report of 2019 Mini EDHS[[29](#_ENREF_29)], the margin of error of 5%, 95% confidence interval, 1.31 design effect. Based on the above information, the estimated sample size is 392 (ANC), 508 (births attended in a health facility), and 457 (PNC). The sample size needed for identifying the predictors associated with MHSU is calculated considering variables significantly associated with MHSU based on previous studies done in Northern Ethiopia [7], in rural Haramaya district, Eastern Ethiopia [10], and in Northwest Ethiopia [11]. For all calculations, power was set at 80%, level of confidence at 5%, and the ratio of unexposed-to-exposed were assumed to be 1. Hence, the sample size of 1,104 obtained from the second objective will be utilized due to it is the maximum sample size assessed and would be adequate to assess all objectives of this study. The minimum required sample size for the qualitative study will be determined according to the recommendation of Morse and Creswell for Phenomenological studies (20 in-depth interviews, 9 focus group discussions, and 20 key informant interviews) [[30](#_ENREF_30)]. The minimum required sample size for the third and fourth objectives is calculated based on the following considerations. Due to the lack of the previous cRCT on the same topic, assumptions on the proportion of women with knowledge on ODS in the control and intervention arms were taken from a previous quasi-experimental study. The proportion before the intervention was taken as the proportion in the control arm and the proportion after the intervention as the proportion in the intervention arm. Accordingly, P1 = 45.7% (proportion of women’s knowledge regarding ODS during pregnancy) in the control group, P2= 62.9% (proportion of women’s knowledge regarding ODS during pregnancy in the intervention arm) [[14](#_ENREF_14)], 95% CI, and 80% power. According to the above considerations, the estimated effective sample size for individual-based randomization is 286. For this objective, the sample size is adjusted to non-response rate (NRR) by dividing the initial sample size by the anticipated response rate. In case of knowledge regarding ODS during pregnancy, the adjusted sample size to NRR is 286/1 = 286.The minimum required number of clusters is computed by multiplying the effective sample size and ICC factors for both groups [28]. We received the typical value of ICC factor of 0.01 from range values (0.01 to 0.05) based on the existing recommendation [26]. Consequently, the minimum needed cluster number is 329*0.01 = 3.29 for both groups. Nevertheless, to maintain the sufficiency of the cluster and to have adequate power [26, 28], 12 clusters (*12 kebeles*) will be included in this study. To account for the effect of the cluster, the effective sample size is multiplied by a VIF of 1.26. The VIF is calculated with the assumption of an equal cluster size of 27 study subjects from 12 clusters (*kebeles*). Using ICC value of 0.01, (VIF = 1+ [(n-1) ICC]), where ‘n’ is the average cluster size [28]. Thus, the final estimated sample size is 360 (180 in the intervention arm and 180 in the control arm). However, the sample size calculated for the fourth objective which is designed to evaluate the effect of the intervention on MHSU is 1,126 (i.e., larger). Hence, the sample size of 1,126 obtained from the fourth objective will be utilized for this objective as well as it would be maximum or representatives of the sample for both objectives.

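### Cluster handling in a kebele-randomised trial is contradictory: the multilevel model hangs on an ICC or chi-square pre-test, the named between-arm test is a plain t-test, and other sentences promise cluster models without condition

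*Protocol*

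**What the plan says.** Under Study design, the protocol describes a two-arm cluster trial with the kebele as cluster: "The study is a 2 arm CRCT, with every cluster being" a kebele.

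Under Sample size calculation, it plans for clustering: "We received the typical value of ICC factor of 0.01 from range values (0.01 to 0.05"). It assumes an "equal cluster size of 27 study subjects from 12 clusters", and then: "To account for the effect of the cluster, the effective sample size is multiplied by a VIF of 1.26".

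Under Statistical data analysis, three strands sit together.

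- **A conditional rule.** "The multilevel analysis will be considered if the calculated value of ICC is greater than 5" per cent. Next, "we will decide whether or not the multilevel model is required by doing a random intercept model". Finally, "If the chi-square test is significant or the ICC value is greater than 5%, the multilevel analysis model is mandatory to consider".
- **Unconditional statements.** The same section says that bi-variable and multivariable analyses will use generalized mixed models with random effects. It also says that GEE or multilevel regression will deal with between- and within-cluster variation in the adjusted analysis. The Summary says multilevel linear regression will be used for danger-sign knowledge and for birth preparedness and complication readiness.
- **A plain test between arms.** The section ends by naming an independent t-test that compares mean change between arms for knowledge, preparedness and service use. It has no cluster term. The Summary also names paired and independent t-tests for the intervention effect.

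The section sets the significance level at 0.05/3 = 0.017.

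**The concern.** When kebeles are randomised, the arm comparison has to carry between-kebele variation whatever the estimated ICC turns out to be. A small or non-significant estimate from 12 clusters does not show that women are independent. The threshold is also badly placed: 5% is five times the planning value and equals the top of the protocol's own range. The sample size is inflated for an ICC of 0.01, while the ICC trigger would treat that same value as ignorable.

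The t-test raises a separate problem. It ignores kebele at any ICC, and the pre-test does not govern it.

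Two analysts could follow this section and run different main analyses, one with kebele and one without. The analysis without it gives intervals that are too narrow and too many false claims that health education works.

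**Working it through.** **Inputs.** From Sample size calculation: planning ICC 0.01 (range 0.01 to 0.05), 12 clusters, planned cluster size 27, proportions 45.7% and 62.9%, 80% power, individual-level total 286, final total 1,126. From Statistical data analysis: ICC threshold 5%, significance level 0.017.

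**The plan's own figures.** Two proportions, 45.7% against 62.9%, two-sided 5%, 80% power, with continuity correction: 142 per arm, 284 in total, within 2 of the stated 286. VIF = 1 + (27 − 1) × 0.01 = 1.26. Then 286 × 1.26 = 360.4, the stated 360. The 1,126 for service use cannot be rebuilt, because its inputs are not given.

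**Design effect at the size to be used.** Spread equally, 1,126/12 = 93.8 women per kebele. Design effect = 1 + (93.8 − 1) × ICC:

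- ICC 0.01: 1 + 92.8 × 0.01 = 1.93
- ICC 0.03: 1 + 92.8 × 0.03 = 3.79
- ICC 0.05: 1 + 92.8 × 0.05 = 5.64

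**Plain t-test, clustering ignored.** Type I error = 2 × (1 − Φ(z/√design effect)), with z = 1.96 at 5% and 2.387 at 0.017. At ICC 0.01 and nominal 5%: 1.96/√1.93 = 1.41, giving 15.8%. At 0.017: 2.387/√1.93 = 1.72, giving 8.6%. The other ICCs are in the table.

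**Two-trigger rule.** This was simulated with no true effect: 12 equal clusters, 6 per arm, 94 women each, Gaussian outcome. The chi-square was read as the likelihood-ratio test of the random intercept at 5%. If either trigger fired, a cluster-level t-test on 10 df was used; otherwise the ordinary t-test. Ranges cover a random intercept model without and with an arm term. A repeat with 60,000 trials per setting agreed.

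| True ICC | Clustering not modelled | Two-trigger rule: type I at 5% | at 0.017 | Plain t-test: type I at 5% | at 0.017 |
|---|---|---|---|---|---|
| 0.01 | 58–67% | 8–11% | 3–6% | 15.8% | 8.6% |
| 0.03 | 10–16% | 6–8% | 2–4% | 31.4% | 22.0% |
| 0.05 | 2–4% | 5–6% | about 2% | 40.9% | 31.5% |

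A cluster-level t-test applied unconditionally held 5% and 1.7% in every row.

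**Which trigger does the work.** At ICC 0.01 and 94 per kebele, the estimated ICC exceeds 5% in under 0.1% of trials, so nearly all the protection comes from the chi-square.

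**At the planned 27 per kebele** (ICC 0.01, design effect 1.26), the rule leaves clustering unmodelled in 90–93% of trials. Ignoring clustering there gives 8.1% at nominal 5% and 3.3% at 0.017.

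**The case against.** The strongest reply is that the plan does not drop clustering. The unconditional sentences on mixed models, GEE and multilevel regression stand in the protocol, and GEE is never made subject to the pre-test. This part stands. A reader might infer that clustering will be modelled only if a trigger fires; the text does not support that, and the accurate description is contradiction. But the unconditional sentences do not settle the matter. Neighbouring text concerns screening and adjustment for predictors of service use, and the arm comparison is given to a plain t-test.

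Scope is a fair second point. The pre-test sits between the wealth index and the predictor screening, which is largely Paper I material. The section neither confines it to Paper I nor applies it expressly to Papers III and IV. As the only analysis section for all four papers, it leaves this open.

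Third, a reader might judge the rule by the ICC threshold alone and expect error rates close to those of ignoring clustering, including at ICC 0.03. That is not the stated rule. With the chi-square clause the excess at 0.03 to 0.05 is small.

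Fourth, the chi-square test is not defined. An ANOVA F-test in its place would detect clustering in about half of trials at ICC 0.01 (49–52%), against 33–42% for the likelihood-ratio test. Missed detections would remain common.

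Finally, small-sample corrections and degrees of freedom are commonly left to a SAP. The protocol does not say that GEE would be uncorrected, so no fault is claimed there.

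**Conclusion.** The point holds as contradictory cluster handling in a cluster-randomised trial. It is not a matter left to a SAP: the protocol fixes a rule and a test, and neither suits the design.

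Harm from the pre-test is concentrated near the protocol's own planning ICC, where type I error is roughly two to three times the 0.017 level. That undoes much or all of the Bonferroni protection. The plain t-test is invalid at every ICC above zero and worsens as the ICC rises.

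The figures assume equal clusters, all 1,126 women in the 12 kebeles, a Gaussian outcome, a likelihood-ratio reading of the chi-square, and an ICC that applies to the variable analysed, here the change score. The direction does not depend on these assumptions; the exact percentages do. The analysis should be corrected before any arm comparison is run.

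**What to change.** For Papers III and IV:

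1. Delete the ICC and chi-square triggers.
2. Replace the plain independent t-test between arms. Deleting the triggers alone would leave it in place.
3. State that every arm comparison accounts for kebele whatever the estimated ICC, by a method valid for 12 clusters. Examples are a t-test on the 12 kebele summaries with 10 df, or a mixed model or GEE with a small-sample correction.
4. Report the ICC as a result; do not use it to choose the model.
5. Bring the Summary and Statistical data analysis into line, and say which sentences apply to the Paper I survey only.

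This changes wording only, with no new data and no change to trial conduct. The cost is wider confidence intervals, which reflect the information that 12 kebeles actually carry.

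### With 12 kebeles and no small-sample inference named, z-based GEE or multilevel tests of the arm effect would run at about 7–10% for a nominal 5% and 3–5.5% for a nominal 1.7%

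*Protocol*

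**What the plan says.** The Protocol's Study design section randomises kebeles. Its Sample size calculation section fixes their number: "12 clusters (*12 kebeles*) will be included in this study", chosen "to maintain the sufficiency of the cluster and to have adequate power". The same section sets the trial total: "Hence, the sample size of 1,126 obtained from the fourth objective will be utilized for this objective". It takes the intracluster correlation from a range: "We received the typical value of ICC factor of 0.01 from range values (0.01 to 0.05) based on the existing recommendation".

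The Statistical data analysis section says: "The Generalized Estimated Equations (GEE) or multilevel regression models will be utilized to adjust for between and within-cluster variation for adjusted analysis". It works at 95% confidence or the 5% level, then divides by three outcomes: "Thus, a statistically significant association will be declared when p-value less than 0.017".

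The Methods paragraph of the Summary assigns multilevel linear regression to danger-sign knowledge and birth-preparedness practice, and GEE to the predictors of maternal health service use.

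The protocol names no small-sample variance correction, t reference distribution, degrees-of-freedom method or permutation test for these models. Nor does it say that normal-theory inference will be used.

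**The concern.** In a cluster-randomised comparison, the information on the arm effect comes from the clusters. GEE with a sandwich variance, and multilevel models judged by Wald z-tests, are justified when there are many clusters. With 12 there are two faults. A normal quantile is used where a t quantile on about 10 degrees of freedom is needed. In addition, the uncorrected sandwich, or the maximum-likelihood variance, is too small on average.

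The 0.017 threshold is there to keep the chance of any false claim across three outcomes near 5%. Relative error grows in the tail, so the shortfall is proportionally worse at 0.017 than at 0.05.

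This matters even though the same section has larger problems: a woman-level independent t-test for the arm comparison, and a multilevel model used only if the ICC exceeds 5% or a chi-square test is significant. The natural repair is to use the plan's own GEE or multilevel model throughout. That alone would not restore the stated error rate.

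**Working it through.** **Inputs from the Protocol.** 12 kebeles; 1,126 women (563 per arm); ICC 0.01 from a range of 0.01–0.05; levels 0.05 and 0.017.

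**Assumptions.** 6 kebeles per arm; equal cluster sizes; the 12 kebeles also carry the 1,126 women, so 1126/12 ≈ 94 per kebele; outcome proportion 0.48 in the simulations.

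**Reproducing the plan's figures.**
- Proportions 45.7% and 62.9%, two-sided 5%, 80% power: 142 per arm with continuity correction, 284 in total, close to the stated 286 (131 per arm, 262 in total, without it).
- VIF = 1 + (27 − 1) × 0.01 = 1.26; 286 × 1.26 = 360.4, stated as 360.
- 0.05/3 = 0.0167, stated as 0.017.
- The 1,126 cannot be reproduced, because its inputs are not shown; it is used as given.

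**Analytic size.** Degrees of freedom for the arm effect: 12 − 2 = 10. With equal clusters the uncorrected sandwich estimates the variance too low by (6 − 1)/6 = 5/6. The two-sided normal quantiles are 1.960 (5%) and 2.387 (1.7%).

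| Variance used, judged by z | Formula | Size at 5% | Size at 1.7% |
|---|---|---|---|
| Unbiased | P(\|t10\| > z) | 0.078 | 0.038 |
| Sandwich × 12/11 | P(\|t10\| > z√(10/11)) | 0.091 | 0.046 |
| Uncorrected sandwich | P(\|t10\| > z√(5/6)) | 0.104 | 0.054 |

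**Simulation.** 100,000 beta-binomial trials per setting, 94 women per kebele, ICC 0.01 to 0.05. The multilevel rows use a closed-form linear random-intercept approximation with the variance component truncated at zero.

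| Method | Size at 5% | Size at 1.7% |
|---|---|---|
| GEE, uncorrected sandwich, z | 0.101–0.103 | 0.052–0.054 |
| GEE, sandwich × 12/11, z | 0.088–0.090 | 0.044–0.046 |
| Multilevel, ML, z | 0.090–0.104 | 0.044–0.055 |
| Multilevel, REML, z | 0.072–0.079 | 0.033–0.039 |
| Variance × 12/10, t on 10 df | 0.048–0.050 | 0.017 |

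Relative to nominal, the z-based rows are about 1.4 to 2.1 times too high at 5% (0.072/0.05 to 0.104/0.05) and about 1.9 to 3.2 times at 1.7% (0.033/0.017 to 0.055/0.017).

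**Family-wise error, three independent tests at the 0.017 threshold.**
- Intended: 1 − (1 − 0.017)³ = 0.050.
- REML at its lowest: 1 − (1 − 0.033)³ = 0.096.
- Uncorrected GEE: 1 − (1 − 0.054)³ = 0.153.

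**Sensitivity to cluster size.** With 30 women per kebele and ICC 0.01, close to the 27 per kebele used for the third objective, the multilevel z-tests are nearer nominal: 0.054 (REML) and 0.064 (ML) at 5%. The GEE rate barely moves (0.101). The multilevel figures therefore depend on the larger trial size being spread over the same 12 kebeles.

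**The case against.** The strongest objection is that this argues from silence. A confidence interval and a p-value can be t-based and corrected as easily as z-based, and the choice of correction is often left to a statistical analysis plan, which is not at hand. That stands to this extent: a reader might infer that the protocol commits to large-sample inference and that its true false-positive rate is double the stated one. The text supports neither. The rates above apply only if the named methods are run with z-based inference and no correction.

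The objection does not dispose of the point. The section already fixes fine detail: the p<0.25 screening rule, the method of variable entry, collinearity limits and a threshold to three decimals. The protocol also presents 12 clusters as sufficient. Following the named methods in their usual form would miss the error rate that it sets.

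Three further limits are accepted:
- The Summary ties GEE expressly to predictors of service use, and the rule on adjusted odds ratios is worded for predictors. The number of kebeles in that survey is not given, so the 10-df argument cannot be carried over to it.
- A family-wise error of 15% for the whole trial is tempting, but it applies the uncorrected GEE rate to all three outcomes. Knowledge and birth preparedness are assigned to multilevel linear models; with REML the independent-test figure is nearer 10–11%.
- The unclustered t-test and the ICC rule are larger faults. Ignoring clustering gives a simulated size of 0.16 at ICC 0.01 and 0.42 at ICC 0.05 for nominal 5%. They are separate from this one.

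**Conclusion.** The concern holds in conditional form and should be acted on. If the trial's arm effect is tested by z-based GEE or multilevel models on 12 kebeles, type I error is about 7–10% at nominal 5% and about 3–5.5% at nominal 1.7%. The Bonferroni threshold would then not hold family-wise error near 5%: independent outcomes give about 10–15%, correlated outcomes somewhat less. A single summary of twice the nominal rate fits GEE with an uncorrected sandwich at 5%. It overstates REML at 5% and understates GEE at 0.017.

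The conclusion rests on 6 kebeles per arm, equal cluster sizes and about 94 women per kebele, none of which the protocol states. It covers the arm comparison only.

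**What to change.** State in the Statistical data analysis section that every trial arm comparison, whatever the estimated ICC, accounts for kebele and uses small-sample inference. Either of these would serve:
- a multilevel model fitted by REML with Kenward-Roger degrees of freedom; or
- GEE with a bias-corrected sandwich (Mancl-DeRouen or Kauermann-Carroll) and a t reference on about 10 degrees of freedom.

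Reduce the degrees of freedom for kebele-level covariates. Place of residence is a listed covariate and the Study area section classes kebeles as urban or rural, so it may use one. Add a t-test on the 12 kebele-level summaries as a check. If a statistical analysis plan already contains such a rule, a cross-reference is enough.

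The change is to analysis wording only. At 95% confidence the critical value rises from 1.96 to 2.23, so intervals are about 14% wider than z-based REML intervals (2.228/1.960 = 1.137). They are about 25% wider than uncorrected GEE intervals (1.137 × √(6/5) = 1.245). Power falls somewhat. The third-objective calculation, at "95% CI, and 80% power", makes no allowance for this, so the stated power should be rechecked.

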**The study variables**

| Outcome variables | Definition |
| --- | --- |
| MHSU | Utilization of maternal health care measured using the yes or no questions at the baseline and after 6 months of intervention. |
| Knowledge of obstetrics danger signs | Will be measured by using the 30 knowledge assessment questions. |
| Birth preparedness and complication readiness practice | Will be assessed using the 5 practice assessment questions. |
| Perceptions, barriers, and facilitators | Perceptions, barriers, and facilitators of MHSU that affect the utilization of MHS will be explored qualitatively. |
| Exposure variable | Definition |
| Health education | **Intervention group:** will receive routine plus pre-recorded audio-based HEI package for six months until date of delivery.  **Comparator group:** will receive the routine health education package for six months until the date of delivery as per the Ethiopian guidelines. |
| Predictors | Predictors that predict the utilization of MHS. It will be measured retrospectively. Socio-economic and demographic, obstetric characteristics, health facility and socio-cultural related predictors. |
| Covariates | Place of residence (urban/rural), educational status of women and her spouse, wealth index, maternal age, occupational status of women and her spouse |

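### The p < 0.25 bivariable screen for the MHSU predictor model can remove masked confounders, and the protocol's own named covariates are not exempt from it

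*Protocol*

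**What the plan says.** The Protocol, Statistical data analysis, sets the entry rule for the MHSU model: "Those variables with p-values < 0.25 on the bi-variable analysis model will be included in a multivariable regression model". It gives the purpose as "to find out predictors independently associated with MHSU adjusting for other variables in the model". Variables that pass are not pruned further: "The candidate variables will be entered into the multivariable regression model using the ENTER regression method". Confounding is left to the same modelling step: "The stratified and multivariable analyses will be used to control for the potential confounding variables". Adjusted odds ratios are then read from ordinary intervals: "A statistically significant association between the variables of interest will be confirmed when the 95% CI of the AORs did not contain 1". The section also gives a Bonferroni level: "the adjusted level of significance is 0.05/3 = 0.017".

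The study variables table has two relevant rows. Covariates names seven items: "Place of residence (urban/rural), educational status of women and her spouse, wealth index, maternal age, occupational status of women and her spouse". Predictors is given only as groups, among them "obstetric characteristics, health facility and socio-cultural related predictors". The protocol does not say whether the seven covariates go through the screen or are kept regardless of it.

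**The concern.** The screen asks whether a variable is associated with the outcome on its own. Confounding control asks whether leaving the variable out changes another variable's estimate. The two answers can differ. If a variable lowers service use but is positively correlated with one that raises it, its crude association can be close to zero. It then fails the screen, and the estimate for the variable that stays is biased.

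As written, wealth, education or residence could leave the MHSU model this way, although the protocol has already named them. The interval from the final model is computed as if its variables had been fixed beforehand, so it does not reflect the selection. At stake are the adjusted odds ratios and the list of independent predictors in Paper I, whose stated objective is to identify predictors of utilization.

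**Working it through.** **Inputs from the Protocol, Sample size calculation:** n = 1,104 for the survey; anticipated use 74% (antenatal care, ANC), 48% (facility birth) and 34% (postnatal care, PNC); margin 5%; design effect 1.31.

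**1. The plan's own figures.** n = 1.31 × 1.96² × p(1 − p) / 0.05² gives 388, 503 and 452. The protocol states 392, 508 and 457. All agree to about 1%, so the proportions and design effect can be used below. The inputs behind 1,104 are not given, so that figure is taken as stated.

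**2. Why a masked confounder fails the screen.** Take two standardised predictors with log odds ratios b1 and b2 and correlation r. To a linear approximation:
- crude slope of the second = b2 + r·b1
- slope of the first when the second is omitted = b1 + r·b2

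With assumed odds ratios (OR) 1.42 and 0.84 and r = 0.5:
- second, crude: −0.174 + 0.5 × 0.351 = 0.001, so p ≥ 0.25 in about 75% of samples by definition
- first, second omitted: 0.351 − 0.5 × 0.174 = 0.264, an OR of 1.30 instead of 1.42

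**3. Simulation.** Logistic model, n = 1,104, crude screen at p < 0.25, then all survivors entered. Rows at 48% use have two predictors. Rows at 34% use add ten null predictors. All effects and correlations are assumptions.

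| Scenario | True ORs | Use | r | Second dropped | Mean OR, first | Coverage after screen |
|---|---|---|---|---|---|---|
| Full masking | 1.42, 0.84 | 48% | 0.5 | 76% | 1.33 | 77–79% |
| Full masking | 1.65, 0.78 | 48% | 0.5 | 77% | 1.50 | 57–59% |
| Full or nearly full | 1.50, 0.80–0.82 | 34% | 0.5 | 72–76% | 1.39 | 71–72% |
| Partial | 1.42, 0.92 | 48% | 0.5 | 37% | 1.38 | 89% |
| Partial | 1.42, 0.75 | 48% | 0.5 | 24% | – | 85% |
| Slight | 1.42, 0.70 | 48% | 0.5 | 4% | – | 93% |
| Same direction | 1.42, 1.10 or 1.19 | 48% | 0.5 | 0% | 1.42 | 95–96% |
| Same direction | 1.50, 1.30 | 34% | 0.3 | 0% | 1.51 | 95% |

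The full model kept 94–96% coverage wherever it was compared. With two weak effects (OR 1.15 with 1.10 or 0.83; 34% use, r = 0.2 or 0.4) the second was dropped in 19–20% of runs and coverage was 93–97%. In the 1.50 and 0.80 case the mean reported standard error was 0.069, against an actual standard deviation of 0.081.

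**4. Null predictors.** Among null predictors that passed the screen, 19–22% had a 95% interval excluding 1. About a quarter pass, so the rate over all null predictors examined is roughly 0.25 × 0.20 = 5% to 0.25 × 0.22 = 5.5%; the simulated overall rate was near 6%.

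**5. Can the sample carry a model without the screen?** Women in the smaller outcome class at 1,104, and after division by 1.31:
- ANC: 1,104 × 0.26 = 287; 219
- facility birth: 1,104 × 0.48 = 530; 405
- PNC: 1,104 × 0.34 = 375; 287

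At 10 per parameter, a common rule of thumb, ANC is the tightest: about 21 parameters after the design effect. If the seven covariates need 15 to 20 parameters once categories are coded (an assumption), ANC has 219/20 = 11 to 219/15 = 14.6 per parameter.

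The 74% may be too high for the ANC outcome under The measurements, which also requires an early visit, iron-folic acid, tetanus toxoid and laboratory results. If composite use were 10–20% (an assumption), the smaller class would be 110–221, or 84–169 after the design effect, which supports 8–16 parameters.

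**The case against.** **The masked case is chosen to be the worst.** In the full-masking settings the two effects cancel almost exactly, and nothing in the protocol says its variables behave like that. This stands. A reader might infer that the reported intervals are always too narrow; the simulations do not support that, since same-direction confounders are kept and lose no coverage. What remains is that the analyst cannot see from a crude p-value which case applies.

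**The screen is lenient, and survivors are not pruned.** True, and this limits the harm. The 19–22% figure for surviving null predictors might be read as a large inflation of false positives, but over all null predictors examined the rate stays near the nominal 5%.

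**The rule is not about the trial.** Largely correct. The screening sentence gives its purpose as finding predictors of MHSU, which is the Paper I objective, and the arms are compared separately by t-tests under intention-to-treat. A reader might infer that the trial's main comparison depends on the screen; the text does not say so. Nor is an unnamed covariate set for an adjusted trial analysis a fault here, since that can sit in the statistical analysis plan.

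**The Covariates row may never have been meant for the screen.** Possible: Predictors and Covariates are separate rows. It therefore goes too far to say that the screen overrides a fixed adjustment set. The supportable statement is that no exemption is written.

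**Which obstetric variables?** A reader might take the predictor groups to mean that parity and gestational age at enrolment are listed as collected. The protocol names neither, so the fix cannot rest on them.

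**Capacity for a full model is unproven.** This stands for the whole predictor list, which is not itemised. A count of 28 parameters for ANC (287/10) would ignore the protocol's own design effect.

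**Conclusion.** The concern holds for the MHSU predictor model, mainly in Paper I. The protocol uses a crude p-value to decide which variables enter a model it also relies on for confounding control, and it does not protect its own seven covariates. The harm is conditional on assumed effects and correlations:
- full masking: the confounder is dropped in about 75% of surveys, and coverage of the remaining predictor is 57–79%
- partial masking: coverage about 85–90%
- same-direction effects: no harm

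The sample does not require the screen for the seven covariates at the anticipated proportions. ANC is the tightest, at about 21 parameters after the design effect, and fewer if the composite definition makes ANC use uncommon. The rule should be changed because the replacement is better and cheap. It does not threaten the randomised comparison as the protocol describes it.

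**What to change.** In Statistical data analysis:
1. Delete the p < 0.25 entry rule.
2. State that the seven covariates named under The study variables enter the MHSU model regardless of their p-values.
3. Itemise the other Paper I predictors in advance on subject-matter grounds and enter them together. Size the list to the data: about 21 parameters in total for ANC at 74% use, recalculated if the composite ANC definition gives a lower proportion. If space is short, use fewer parameters per variable or a shorter list fixed in advance, not a crude test.
4. If an adjusted trial analysis of MHSU is done, use the same seven covariates for every outcome and do not apply the screen.

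The cost is protocol wording, the work of writing the predictor list, and slightly wider intervals where weak predictors stay in. Data collection and sample size are unchanged.
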